#### 6.1.2 Investigations at screening visit

Randomisation (week 0) should take place no more than four weeks after the screening visit and ideally as soon as possible after eligibility has been confirmed. At the screening visit a trial number will be assigned and used on all paperwork and labels. A clinical assessment should be completed and the participant and/or carer should complete an adherence questionnaire according to age and knowledge of HIV diagnosis (see flow sheets 1.9, 1.10, 1.11 and 1.12).

Blood will be taken for haematological and biochemical investigations, T cell subsets (including RO/RA phenotype if available), measurement of HIV-1 RNA viral load (the same assay should be used at least throughout the pilot phase and ideally throughout the whole trial, although the assays used may vary across centres according to clinical practice and management), and for plasma and cell storage (if the participant attends a clinical centre where this is possible).

As soon as the biochemistry and immunological/virological results are received and eligibility has been confirmed, the screening form with confirmation of eligibility and receipt of informed consent, clinical history and assessment, haematology, biochemistry and HIV-1 RNA viral load should be faxed to the appropriate Trials Unit.

## 6.2 Week 0 visit and randomisation procedure

### 6.2.1 All participants

The eligibility criteria and consent should be re-confirmed verbally and noted on the Randomisation Form. If the parents/carers and/or participant are prepared for Short Cycle Therapy to commence at this visit, contact the appropriate Trials Unit to enrol the participant (see General Information, 'Randomisations & SAE notifications' section at the front of the protocol for telephone and fax numbers). The Trials Units will inform the sites of the young person's allocation immediately (continuous ART or Short Cycle Therapy 5-on / 2-off strategy), which should be entered on the trial register.

A clinical assessment should be completed which will include measurements of height, weight, presence of adverse events, change in HIV disease stage and ethnic origin. The following investigations are to be performed: haematology, biochemistry, glucose and lipid profile (fasting), T cell subsets (plus RO/RA phenotype if available). Blood should be taken for plasma storage (plus cell storage if the participant attends a clinical centre where this procedure is possible or where a courier can be arranged). A quality of life questionnaire (PedsQL™) should be completed for all participants (and carers) and an acceptability questionnaire for those young people randomised to SCT (and carers) (see flow sheets 1.9, 1.10, 1.11 and 1.12). Participants should be given a diary to record when they have taken their ART, which will include a reminder to re-start therapy after the 2 days off ART in the SCT arm (Appendix 7). The diary will be anonymised by the clinical centre staff before being sent to the Trials Units.

For further details on specific requirements for the week 0 visit and randomisation procedures see sections 7.1, 7.3 and 7.6.

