**1.11 FLOWSHEET FOR MAIN PHASE OF STUDY: SCT arm (after pilot fully recruited)**

| WEEK                                              | Screening
-4 to -2 | Randomisation
0 | 4 | 12  | 24  | 36  | 48 | Further follow-up             | End of study visit |
|---------------------------------------------------|-----------------------|--------------------|---|-----|-----|-----|----|-------------------------------|--------------------|
| SCT arm                                    |                       |                    |   |     |     |     |    |                               |                    |
| Signed informed consent                           | X                     | (confirm)          |   |     |     |     |    |                               |                    |
| Clinical assessment a                  | X                     | X                  | X | X   | X   | X   | X  | Every 12 weeks                | X                  |
| Tanner scales                                     |                       | X                  |   |     | X   |     | X  | Every 24 weeks                | X                  |
| Lipodystrophy assessment                          |                       | X                  |   |     | X   |     | X  | Every 48 weeks                | X                  |
| Local HIV-1 RNA viral load                        | X                     |                    | X | X   | X   | X   | X  | Every 12 weeks                | X                  |
| T cell lymphocyte subsets
inc. RO/RA phenotype | X                     | X                  | X | X   | X   | X   | X  | Every 12 weeks                | X                  |
| Biochemistry b                         | X                     | X                  |   | (X) | (X) | (X) | X  | As per local practise         | X                  |
| Haematology c                          | X                     | X                  |   | X   | X   | X   | X  | Every 12 weeks                | X                  |
| Lipids/glucose d                       |                       | X                  |   |     | X   |     | X  | Every 48 weeks                | X                  |
| Pregnancy Test e                       | X                     |                    |   |     | X   |     | X  | Every 24 weeks                | X                  |

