Data on viral dynamics in the first few days following treatment cessation are scarce. Jacobsen *et al* in a 4-arm study of PTI  $\pm$  HIV immunisation reported viral rebound to >50 c/ml following treatment interruption at a median (interquartile range) of 15 (8 to 31) days for those with prior PTI and of 21 (13 to 30) days for those without prior PTI [24]. Harrigan *et al*, whilst assuming a constant rate of viral increase that starts as soon as the patient stops therapy, suggest that many patients stopping therapy (previously suppressed) will have increases in plasma viral HIV RNA of about 0.2 log/day and will only reach detectable levels (>50 c/ml) within 1 to 2 weeks of stopping therapy [34].

A substudy of PENTA 11 evaluated the pharmacokinetics, viral load rebound and resistance profiles in 35 children stopping non-nucleoside reverse transcriptase inhibitor (NNRTI) based ART [35]. 21 children followed a staggered stop (SS) strategy whereby the NNRTI (NVP or EFV) was stopped at randomisation and the remaining 2 NRTI drugs stopped 7-14 days later, and 14 children followed a replacement strategy (RS) whereby the NNRTI was replaced with a PI and all drugs stopped 7-

14 days later. Results of HIV viral load testing in 8 children following SS and 7 following RS strategies show that the majority of children still had undetectable HIV RNA 5-8 days after stopping all drugs (minimum 12 days after stopping the NNRTI) (Table 1). No NNRTI resistance mutations were detected in any of the children in the substudy.

**Table 1: Viral loads (c/ml) 5-8 days after 1st interruption, stopping ALL drugs in 15 children in the PENTA 11 PK substudy**

| Strategy | NNRTI | Days after stopping ALL drugs |     |                   |     |
|----------|-------|-------------------------------|-----|-------------------|-----|
|          |       | 5                             | 6   | 7                 | 8   |
| SS       | EFV   | <50                           |     |                   | <50 |
|          | NVP   | <50, <50                      | 159 | <50, 89, 7000     |     |
| RS       | EFV   |                               |     | <50               | <50 |
|          | NVP   |                               |     | <50, <50, 52, 707 | 70  |

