### 8.5 Cells and Plasma for storage

6ml of EDTA blood will be collected throughout the trial for plasma storage for viral load testing and analyses as part of the virology/immunology substudy (Appendix 11), and other HIV related tests as appropriate. Plasma will be stored at weeks -4 to -2 (screening), week 0 (randomisation), 4, 8 (pilot only), 12, 24, 36 and 48 from all participants in both arms. Plasma will also be stored at weeks 1, 2 and 3 for participants in the pilot phase. (See flowsheets)

In addition, in centres who have capability, cells from all participants will be stored at weeks -4/-2 (screening), 0, 4, 12, 24, 48 and every 24 weeks until the end of the trial at  $-80^{\circ}\text{C}$  for subsequent assessments as part of the virology/immunology substudy (see Appendix 11). An extra 10ml of whole blood is required at the time points for cell storage.

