## 11.3 Sample size

This phase II/III trial will enrol a minimum of 160 young people, at least 80 per arm.

Assuming 90% of young people in the continuous ART arm and in the SCT arm maintain HIV-1 RNA  $< 50$  c/ml to week 48, 155 young people will provide at least 80% power to exclude a difference of 12% between the two arms (i.e. to exclude suppression rates of less than 78% in the SCT arm) (one-sided  $\alpha = 0.05$ ) [37]. A minimum of **160 (80 per arm) young people will be enrolled** to allow for loss to follow-up (in previous PENTA trials loss to follow-up has been less than 3%).

The power calculations are based on the assumption that 90% of patients in the continuous ART arm will remain virally suppressed to week 48. Any decrease in this percentage is likely to under

power the study and could lead to an equivocal result, as could other changes to the assumptions. The table below gives an indication of the power to exclude a difference of 12% between the two arms for different sample sizes and levels of suppression in the continuous ART arm:

| Total sample size | Power by level of suppression in control arm |                |                |                |                |                |
|-------------------|----------------------------------------------|----------------|----------------|----------------|----------------|----------------|
|                   | 90% suppressed                               | 89% suppressed | 88% suppressed | 87% suppressed | 86% suppressed | 85% suppressed |
| 160               | 80                                           | 77             | 74             | 72             | 69             | 67             |
| 170               | 82                                           | 79             | 76             | 74             | 72             | 69             |
| 180               | 84                                           | 81             | 79             | 76             | 74             | 72             |
| 190               | 86                                           | 83             | 81             | 78             | 75             | 74             |
| 200               | 87                                           | 85             | 82             | 80             | 78             | 76             |
| 210               | 89                                           | 86             | 84             | 82             | 79             | 77             |

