## **11.6 Analysis plan**

Intention-to-treat analyses will be performed on all randomised participants. Statistical methods include:

- Descriptive statistics for the summary of baseline characteristics
- Fishers exact test and logistic regression models for the analysis of binary outcome variables
- Analysis of variance and linear regression models for the analysis of continuous outcome variables, adjusting for baseline
- Poisson regression for the analysis of the incidence rate of clinical/adverse events
- Log rank test and proportional hazards regression models for the analysis of time to event variables

The incidence rate of clinical/adverse events will be summarised by body system and randomised arm. First events (in terms of time to first event) and all events will be considered.

Major resistance mutations will be defined by the current IAS-USA list.

The primary outcome for the main study is HIV-1 RNA  $\geq 50$  c/ml (confirmed on a separate sample within 1 week) at any of week 4, 12, 24, 36 or 48. This outcome only considers HIV-1 RNA measurements at these time points due to the difference in viral load monitoring in the pilot phase and the main trial. However if a young person enrolled in the pilot phase has an HIV-1 RNA  $\geq 50$  copies/ml at weeks 1, 2 or 3 (reproducible on the same sample) or at week 8 (confirmed on a separate sample within 1 week) they will be considered as reaching the primary outcome at week 4 and 12 respectively. All participants will be analysed in the arm to which they were randomised (intention to treat).

A full Statistical Analysis Plan (SAP) will be developed as a separate document.

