## **APPENDIX 11: VIROLOGY/IMMUNOLOGY SUBSTUDY**

### **Virology**

Proviral DNA will be quantified in all young people at randomisation (week 0) to ascertain whether it can predict response in both arms. To determine whether proviral DNA load differs between arms it will be assayed again in all young people at 48 weeks, and in young people in the SCT arm at 4 weeks. Low level viral loads (<10 c/ml) will also be carried out at the same time points, as well as in young people in the pilot phase of the SCT arm will also be assayed at phlebotomy visits at week 1, 2 and 3 (Monday after interrupting therapy on Saturday/Sunday).

Resistance testing will be performed on all young people who lose virological suppression in either arm at the point of loss of suppression ( $\geq 50$  c/ml), and any subsequent samples with HIV-1 RNA  $\geq 1000$  c/ml. Resistance tests will be performed locally; where this is not possible or the amino acid sequence in FASTA file format cannot be provided, they will be performed centrally.

Therefore, samples will be used to determine if differences in proviral DNA during the study correlate with virological outcome and whether SCT will reduce the subsequent drug options through increased number of drug resistant mutations emerging during the study.

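### No baseline viraemia adjustment is pre-specified for the primary outcome, although a week 0 low-level viral load is already planned in all participants: a minor gain in precision is available at little cost

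*Combined protocol and SAP*

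**What the plan says.** **Week 0 tests.** Section 6.2.1 gives the list as "The following investigations are to be performed: haematology, biochemistry, glucose and lipid profile (fasting), T cell subsets", with no HIV-1 RNA. In the main-phase flowsheets (1.11 and 1.12) the row "Local HIV-1 RNA viral load" is marked at screening and blank at randomisation. The pilot flowsheets (1.9 and 1.10) mark it at both. Screening is at most four weeks before week 0 (6.1.2), and entry requires suppression below 50 c/ml, including at screening (5.1).

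**Stored plasma and planned assay.** Section 8.5 covers all participants in both arms: "Plasma will be stored at weeks -4 to -2 (screening), week 0 (randomisation" and later visits. Appendix 11 plans proviral DNA in all young people at week 0 and adds: "Low level viral loads (<10 c/ml) will also be carried out at the same time points". Read together, these give a week 0 result down to 10 c/ml for everyone.

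**Analysis.** Section 11.6 gives Fisher's exact test and logistic regression for binary outcomes and names no covariate. Baseline adjustment appears only here: "Analysis of variance and linear regression models for the analysis of continuous outcome variables, adjusting for baseline". Detail is left to a separate SAP, whose text is not in the document reviewed. Nothing in the protocol links the week 0 low-level result to the primary comparison.

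**Size of trial.** Section 11.3 starts from "Assuming 90% of young people in the continuous ART arm and in the SCT arm maintain HIV-1 RNA" below 50 c/ml to week 48, and states that "155 young people will provide at least 80% power to exclude a difference of 12% between the two arms", at one-sided 5%.

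**The concern.** The low-level week 0 result is the baseline value of the variable that defines the primary outcome. Everyone must be below 50 c/ml at screening, so a baseline read only at that cut-off has almost no spread. The low-level assay is the one planned viral load measurement that could separate participants at entry. If the result predicts failure, leaving it out makes the interval that must exclude 12 points slightly wider than necessary, and a chance imbalance between arms can move the estimate.

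There is also a pre-specification issue. The trial is open-label, and 11.6 allows logistic regression with unnamed covariates. Naming the covariate and the estimand in advance removes that freedom. The scale matters too: the margin is a risk difference, and an adjusted logistic odds ratio does not address it directly.

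**Working it through.** **1. The plan's own figure.** Inputs from 11.3: 90% suppressed in both arms, margin 12 points, one-sided 5%, 80% power. Unpooled normal approximation:

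- n per arm = (1.645 + 0.842)² × 2 × 0.9 × 0.1 / 0.12² = 77.3, or 154.6 in total. The plan states 155.
- At 80 per arm, SE = sqrt(0.18/80) = 4.74 points. Power = Φ(0.12/0.0474 − 1.645) = 81.2% (the plan's table gives 80). The 90% CI half-width is 1.645 × 4.74 = 7.80 points.

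**2. Effect of adjusting for a two-level baseline.** Let p be overall failure, q the share viraemic at week 0 (>=10 c/ml), and RR their failure risk relative to the rest. Only p is in the documents; q and RR are assumptions.

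- r0 = p/(1 − q + q·RR); r1 = RR·r0
- R² = q(1 − q)(r1 − r0)²/[p(1 − p)]
- adjusted SE = SE × sqrt(1 − R²)

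Example with p = 10%, q = 20%, RR = 3: r0 = 0.0714, r1 = 0.2143, R² = 0.16 × 0.1429²/0.09 = 3.6%. The half-width becomes 7.66 points and power 82.4%. Equivalent N = 160/(1 − 0.0363) = 166, or 6 extra participants.

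Range over q from 5% to 40%, with p = 10% and N = 160:

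| RR | R² | Half-width (points) | Power | Worth in extra participants |
|---|---|---|---|---|
| 1 | 0 | 7.80 | 81.2% | 0 |
| 1.5 | up to 0.5% | 7.78–7.80 | at most 81.3% | under 1 |
| 2 | 0.5–1.4% | 7.75–7.78 | 81.4–81.7% | about 1–2 |
| 3 | 1.7–3.7% | 7.66–7.73 | 81.8–82.4% | about 3–6 |
| 5 | 5.9–8.8% | 7.45–7.57 | 83.2–84.2% | about 10–15 |

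With p = 15%, unadjusted power is 68.5%. It becomes 68.7–69.3% at RR 2, 69.5–70.7% at RR 3 and 72.1–74.1% at RR 5.

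**3. Simulation check (80 per arm, p = 10%).** At q = 20% the variance fell by 1.1%, 3.5% and 8.2% for RR 2, 3 and 5. With RR 1 it rose by 0.6–0.8%. Type I error at the margin was 5.4–5.9% adjusted against 5.2–5.5% unadjusted, a rise of at most about 0.6 points.

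**4. Chance imbalance.** With q = 20%, one SD of the between-arm difference in viraemic share is sqrt(2 × 0.16/80) = 6.3 points. This moves the risk difference by 0.063 × 0.143 = 0.9 points at RR 3 and 0.063 × 0.222 = 1.4 points at RR 5.

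**5. Can >=50 c/ml at week 0 be its own category?** Assume a constant failure rate giving 10% over 48 weeks. The share rebounding in the w weeks between screening and week 0 is 1 − 0.9^(w/48): 0.44% at 2 weeks and 0.87% at 4 weeks, or 0.7 to 1.4 of 160. The chance that one arm of 80 has none is 0.9956^80 = 0.70 or 0.9913^80 = 0.50. The chance that at least one arm has none is 1 − 0.30² = 91% or 1 − 0.50² = 75%. The category would usually be empty in an arm and cannot be fitted separately.

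**The case against.** The strongest reply is that nothing here is wrong. Section 11.6 is silent on covariates; it does not exclude them. It permits logistic regression and hands detail to a SAP. That stands, and the point is limited to what is not pre-specified. It is also fair that the gain is small and rests on assumed inputs, that about 16 expected events support only a very simple adjustment, that the primary analysis would wait on a substudy assay, and that 11.3 already allows recruitment up to 220, which is worth far more power.

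Four stronger readings are tempting and are not supported.

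- **A reader might infer that dropping the local week 0 viral load loses precision.** It does not. Entry already requires <50 c/ml, so a result read at that cut-off would hardly vary. Any gain comes from the assay that Appendix 11 already plans.
- **A reader might infer that participants already at >=50 c/ml at week 0 cannot be identified.** The stored week 0 plasma identifies them.
- **A reader might infer from section 2.4 that residual viraemia is a leading predictor of failure.** It cites a study suggesting that many patients stopping therapy "will have increases in plasma viral HIV RNA of about 0.2 log/day". Over two days that is 10^0.4 = 2.5-fold, so 20 c/ml would reach 50. But the figure assumes growth from the moment of stopping, and the same sentence puts detectability at one to two weeks. Section 2.4 also expects drugs with long half-lives to cover the two days. All four efavirenz values in Table 1, taken 5 to 8 days after all drugs were stopped, are below 50. The primary outcome further requires confirmation on a separate sample within a week, with breaks suspended meanwhile (7.4), so one weekend's rise need not count. The kinetics make a link possible; they do not show it.
- **A reader might infer that rebound between screening and week 0 costs further power.** It falls in both arms by randomisation, and nothing shows that it lies outside the assumed 10% failure.

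**Conclusion.** The point holds as a minor improvement to the analysis plan. The protocol plans a sensitive baseline measurement of the primary outcome variable in every participant but does not say whether the primary analysis will use it.

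At 10% failure and 80 per arm, adjustment is worth 0 to 0.5 power points at risk ratios up to 2, about 1 point at 3 and 2 to 3 points at 5, with a variance cost under 1% if there is no association. These sizes rest on an assumed 5–40% of participants at >=10 c/ml and on assumed risk ratios, none of which the documents give. The sample size of 155 reproduces, and no stated figure is wrong.

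**What to change.** 1. Schedule the Appendix 11 week 0 low-level batch so that results are available before the primary analysis.
2. In 11.6 and the SAP, pre-specify a risk difference (the scale of the 12% margin) adjusted for week 0 viral load as one two-level covariate, <10 against >=10 c/ml. State a simple rule for missing plasma, and do not use a separate >=50 c/ml group. Report it beside the unadjusted difference.
3. Add a sensitivity analysis excluding participants whose week 0 plasma, taken before the first break, was already >=50 c/ml. Because the value precedes the first break, this exclusion does not depend on the strategy.

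The cost is a few lines of text, the timing of one assay batch, and a slight rise in type I error (at most about 0.6 points in simulation). No extra visit, blood draw or assay is needed, and the local week 0 viral load need not be restored.

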## 7 TREATMENT OF PATIENTS

### 7.1 Specific Requirements for the Pilot Phase

At least the first 30 participants enrolled should be willing to stop ART on the Saturday-Sunday and be able to attend the hospital for phlebotomy visits and a blood store at weeks 1, 2, and 3 on the Monday (as the first 15 randomised to the SCT arm will have to attend these weekly phlebotomy visits, those randomised to continuous ART can attend at anytime during the week).

**If any one of the three Monday visits are due to fall on a public holiday please delay enrolment in the trial.**

Participants in the pilot phase should be asked to come to the randomisation visits within 2-4 weeks of the screening visit, having fasted from the previous evening. **Randomisation should only take place when the young person is able to start SCT the following weekend AND attend the subsequent Monday visits.**

Participants in the pilot phase will stop Saturday-Sunday but can change to Friday-Saturday at the end of the pilot phase.

